## Methods/design

### Study aims and hypotheses

The primary aim of this study is to assess the dynamic (3, 6 and 12 months) effects of CPAP on cognitive function, neurocognitive architecture and function. The primary hypothesis of this study is that, compared with the non-CPAP treatment group, patients with OSA who receive CPAP intervention will show improved cognitive function through structural and functional brain modulation immediately after 3 months of CPAP treatment, and that these benefits will persist at the 6-month and 12-month follow-ups. The secondary aims of this study are to investigate whether and which sleep parameters are correlated with improvements of cognitive function, neurocognitive architecture and function; to explore whether the metabolic status assessed by metabolomics can be reversed by CPAP and correlated with improvement of neurocognitive impairment; and to investigate whether CPAP modulates the gut microbiota and contributes to alleviation of neurocognitive impairment. We hypothesise that patients with OSA who undergo CPAP treatment will have metabolic improvement and modulation of gut microbiota, and that these changes will have beneficial effects on neurocognitive impairment.

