### Randomisation, allocation concealment and blinding

All eligible patients with moderate to severe OSA will be randomly and equally allocated (randomisation ratio 1:1) to the CPAP plus BSC group or BSC only group. The central random allocation sequence will be produced using the statistical software SAS V.9.4 and managed by an independent statistician (from the Department of Epidemiology, School of Public Health, Shanghai Jiao Tong University) who will be blinded to the participants’ recruitment, evaluation and intervention. The research assistant from each sleep centre will request (via email) a participant’s allocation from the statistician. The group allocation will not be blinded by participants or intervention supervisors in this trial; however, the patients’ group assignments can be blinded to result assessors and statisticians (ie, which patients are allocated to the CPAP treatment versus BSC groups will not be disclosed).

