#### Secondary endpoints

MMSE.

Default mode network and cortical thickness are measured by functional and structural MRI.

Cerebral metabolites, such as N-acetylaspartate (NAA), choline (Cho), creatine (Cr), glutamate and glutamine and myo-inositol are measured by magnetic resonance spectroscopy (MRS).

Neuropsychological tests will also be performed, including mental arithmetic, memory scanning, movement perception, switching attention, space location memory span and attention allocation choice reaction time curve fit.

Sleep variables include AHI, oxygen desaturation index, lowest oxygen saturation, mean oxygen saturation, micro-arousal index, total sleep time, total REM sleep time, total slow wave sleep time, etc.

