#### Auditory testing

Central auditory processing tests performed include speech-in-noise test, competing sentences test, gap detection and dichotic listening.

Data were recorded using 256-channel high-density electroencephalograph (EEG) recordings.

The gut microbial community will be quantified using metagenomics analysis.^25^ Low-molecular-weight metabolites (≤1000 kDa) will be quantified by metabolomics analysis.^26^

Amyloid-β protein 42, presenilin 1, amyloid-β protein 40, total GSK-3β and serine-9 phosphorylated GSK-3β

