### Sample size calculation

A previous study indicated that the mean and SD of MoCA score are 26.1 (2.0) and 27.4 (2.3) before and after CPAP treatment, respectively.^27^ With a significance level of 0.05 and statistical power of 0.9, the calculated sample size is 59 for each group. Considering a 20% loss to follow-up, a total of 148 participants will be required for randomisation.

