### Statistical methods

The statistical analysis in this trial will be performed using intention-to-treat (ITT). For missing data, a multiple imputation method will be performed. Normality of the data distribution will be examined by the Kolmogorov-Smirnov test. Continuous variables will be expressed as mean±SD or median (first to third quartile) for normal distribution data or non-normal distribution data, respectively. Categorical variables will be expressed as percentages. To assess primary and secondary endpoints in this trial, a mixed-effects linear model under restricted maximum likelihood and a logistic regression model will be used to analyse the effect of CPAP treatment on the continuous or categorical variables, respectively. In each model, the independent variables should include group (CPAP plus BSC group and BSC group), confounding factors (eg, age, BMI and waist:hip ratio, etc), measurement time (eg, baseline and 3-month, 6-month and 12-month follow-ups) or any other inequality factors between groups at baseline assessment. When a significant main effect was observed, a *post hoc* comparison for different time points (eg, baseline and 3-month, 6-month and 12-month follow-ups) or between groups (CPAP plus BSC group and BSC group) will be performed using multiple comparisons. All of the statistical analyses will be performed using SAS V.9.4, with a two-sided p value<0.05 indicating a statistical significance.

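### MoCA has no primary visit or contrast, so the stated 5% error rate and 90% power belong to one comparison that the protocol never names

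*Protocol article*

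**What the plan says.** **Endpoint.** Under Primary endpoints the protocol article lists MoCA alone, with no visit and no contrast. The Outcome assessment section has it measured at baseline and at 3, 6 and 12 months.

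**Hypothesis.** Study aims and hypotheses expects better cognition with CPAP "immediately after 3 months of CPAP treatment, and that these benefits will persist at the 6-month and 12-month follow-ups".

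**Sample size.** The inputs come from an earlier study in which "the mean and SD of MoCA score are 26.1 (2.0) and 27.4 (2.3) before and after CPAP treatment, respectively". The result is one figure: "With a significance level of 0.05 and statistical power of 0.9, the calculated sample size is 59 for each group". Allowing for 20% loss gives 148. No visit is attached to it.

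**Analysis.** Statistical methods specifies a mixed-effects linear model for continuous endpoints, with group, measurement time (baseline among its levels) and covariates as independent variables. Once a main effect is significant, visits or groups are compared post hoc, using multiple comparisons by a method that is not named. The section ends: "All of the statistical analyses will be performed using SAS V.9.4, with a two-sided p value<0.05 indicating a statistical significance".

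**Other outcomes.** The secondary list includes high-dimensional measurements, for example "Default mode network and cortical thickness are measured by functional and structural MRI" and "The gut microbial community will be quantified using metagenomics analysis", together with metabolomics and 256-channel EEG.

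**The concern.** A claim of success on MoCA needs a rule that turns three follow-up visits into one decision. The hypothesis has two parts, an early effect and its persistence, whereas the sample size has one. The document does not say whether success means a difference at 3 months, at any visit, at every visit, or in an average over visits. These rules differ in error rate and power, and the choice could be made after the results are seen.

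The gate in Statistical methods does not close the gap. A main effect of time can be significant when both arms change by the same amount, for instance through practice on the test. A main effect of group, in a model whose time levels include baseline, averages in a visit at which randomisation makes the expected difference zero. The treatment effect at a given visit is a group-by-time contrast, and no such term is listed.

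A second, separate matter is the closing sentence on p<0.05. It fixes a significance criterion for all analyses, and the multiple-comparison wording concerns visits and groups, not the many features within an omics, imaging or EEG family.

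**Working it through.** **1. Reproduce the plan's figure.** Inputs from Sample size calculation:

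- difference: 27.4 − 26.1 = 1.3
- SD: √((2.0² + 2.3²)/2) = √4.645 = 2.155
- significance level 0.05, power 0.90. Sidedness is not given in that section; it is two-sided in Statistical methods.

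Normal approximation: n = 2(1.960 + 1.282)² × 4.645 / 1.3² = 57.8, so 58 per group. With the noncentral t distribution, power is 0.896 at 58 and 0.901 at 59, so 59 per group. A one-sided test would need 48, which does not fit. With 20% loss, 59/0.8 = 73.75, so 74 per group and 148 in all. The stated 59 and 148 are therefore correct for **one** two-group comparison of means at the full two-sided 5%.

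**2. What three visits do to that figure.** The correlation ρ between the visit test statistics is not in the document. It is an assumption, so the range 0 to 0.9 is shown. With 59 per group, each visit's statistic is taken as normal with variance 1 and, where the effect is present, mean 1.3/(2.155 × √(2/59)) = 3.28. The cut-off is 1.96.

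- Any-visit rule, no effect: P(at least one |Z| > 1.96). At ρ = 0 this is 1 − 0.95³ = 0.143.
- All-visits rule, 1.3 points at every visit: P(all three Z > 1.96). At ρ = 0 this is 0.906³ = 0.744, where 0.906 is the normal-approximation power at one visit.

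| ρ | Error, any visit, unadjusted | Power, all three visits |
|---|---|---|
| 0 | 14.3% | 74% |
| 0.5 | 12.5% | 79% |
| 0.7 | 10.9% | 82% |
| 0.9 | 8.4% | 86% |

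**3. The other side of each rule.** The any-visit rule has power of about 95% (ρ = 0.9) to 99.9% (ρ = 0). With no effect at any visit, the all-visits rule gives three significant results in the same direction with probability 0.3% (ρ = 0.5) to 2.2% (ρ = 0.9), below 5%. A single named contrast keeps both 5% and 90%.

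**4. Cost of splitting alpha instead.** Bonferroni at 0.05/3 per visit gives 80.0% power per visit at 59 per group. Restoring 90% needs 76 per group, or 76/0.8 = 95 randomised per group and 190 in all. Naming one contrast avoids this.

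**5. The group main effect.** If the true differences are 0 at baseline and 1.3 at each of three follow-ups, the equally weighted average over the four levels is (0 + 3 × 1.3)/4 = 0.975. That is not the 1.3-point contrast used for the sample size.

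**6. High-dimensional families.** The document gives no feature counts, so the number of false positives cannot be computed. The expected number is 0.05 × m for m features with no effect, for example 5 per 100.

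**The case against.** The strongest reply is that the document does not describe three free tests. MoCA is analysed in one model, comparisons come only after a significant main effect, and multiple comparisons are mentioned. The hypothesis also has a natural order, 3 months first and then persistence, under which the 3-month test keeps 5% and 90%. The article is condensed, and a full protocol or analysis plan could name the procedure.

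Much of this stands, and it rules out three stronger readings:

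- **That every analysis is unadjusted.** The post hoc step is gated and refers to multiple comparisons. The 8–14% applies only if any visit could carry the claim and the unnamed procedure did not adjust. The document states no such rule.
- **That both the 5% and the 90% are lost.** No single rule examined breaks both. The any-visit rule raises the error rate but also raises power. The all-visits rule lowers power but not error control.
- **That the omics, imaging and EEG outcomes erode the primary test.** They are secondary, and leaving them unadjusted changes neither the error rate nor the power of MoCA.

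The choice of correction method for those families is commonly left to an analysis plan, and its absence here is no fault. Some of those aims are also already worded as exploratory.

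The reply does not supply the primary contrast. The visit at which the primary endpoint is judged belongs to the endpoint's definition, and the gate rests on an unspecified main effect. The order in the hypothesis suggests an answer but does not fix one, since the primary aim covers all three visits alike.

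**Conclusion.** The point holds in a limited form. The sample size arithmetic is right, but it powers one two-group contrast that the protocol does not identify, while the hypothesis spans three visits. The 5% and 90% can be claimed only for that one contrast. Depending on the rule adopted later, the error rate could be about 8–14% (any visit, unadjusted) or the power about 74–86% (all visits required). These are alternatives and do not occur together.

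The ranges rest on assumed correlations of 0.9 down to 0 for the error rate and 0 up to 0.9 for power. The power range further assumes 1.3 points at every visit. Both use a two-sample approximation, not the planned mixed model.

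The blanket p<0.05 criterion is a lesser, separate weakness. It limits how far secondary p values in the high-dimensional families can be trusted. No count of false findings can be given from the document.

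**What to change.** In Primary endpoints and Statistical methods:

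1. Name one primary contrast: the CPAP-plus-BSC minus BSC difference in MoCA at 3 months, estimated from the mixed model with a group-by-time term and tested at two-sided 5%.
2. Test 6 months and then 12 months in that fixed order, each at two-sided 5% and only if the preceding test is significant. This follows the order of the hypothesis and needs no division of alpha.
3. Remove the unspecified main effect as a gate for MoCA.
4. In Sample size calculation, state that the 90% power refers to the 3-month contrast alone.
5. Separately, for the microbiota, metabolite, MRI and EEG families, replace p<0.05 with false-discovery-rate control within family (cluster-level control for brain maps), or label the results exploratory.

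The cost is wording. The sample size stays at 148. Some 6-month, 12-month or secondary results may lose nominal significance. Enrolment was still under way when the article was submitted, so at that stage the contrast could have been fixed before results were known.

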### Data collection and management

All of the data collectors and evaluators will be blinded to the group assignments. The data in this trial will be collected using traditional print-based case report forms, which will then be transcribed by a research assistant into web-based case report forms (w-CRFs) with an oracle clinical (OC)/remote data capture (RDC) system (https://clinicaldata.shsmu.edu.cn/). The OC/RDC system will be provided by the School of Public Health of Shanghai Jiao Tong University (Shanghai, China) and will meet the standards of security. Data in w-CRFs will be stored in the OC/RDC system at each of the five research centres separately with password protection. The database incorporates automatic data checking (ie, logic/inaccurate ranges and maintains any changes to the data).

### Ethical issues and dissemination

This protocol will be performed according to the Declaration of Helsinki. Ethics approval (Ethics number: 2015-79) has been obtained from Shanghai Jiao Tong University Affiliated Sixth People’s Hospital. Before enrolment, until a full discussion about risks and potential benefits has been conducted with each participant, written informed consent will be obtained. This study will be published in peer-reviewed journals and presented as oral presentation or poster at conferences in the field of neurology and sleep medicine. Study data will be made available to researchers, healthcare providers and professionals who are on request with the appropriate human research ethics committees’ approvals.

## Discussion

Increasing numbers of clinical studies have shown that CPAP is an effective therapeutic method for neurocognitive dysfunction in OSA. However, the effects and duration of CPAP treatment on neurocognitive function have not been clearly established. This study focuses on the effects of CPAP on middle-aged patients with moderate to severe OSA. Through a 3-month, 6-month and 12-month intervention with CPAP treatment, the results from a range of clinical and biochemical assessments will provide a clearer information on the effects of treatment in OSA.

Measurements of neurocognitive function before and after intervention in this trial may strengthen evidence for links between OSA and neurocognitive dysfunction or reveal new associations. Through CPAP intervention, it will be possible to explore the mechanism of action of CPAP on neurocognitive function (including structural and functional effects), allowing us to investigate the causal relationships between OSA and neurocognitive dysfunction.

The microbial community structure in rodents was altered when the rodents were subjected to intermittent hypoxia or sleep fragmentation.^19 20 28^ In addition, sleep fragmentation-induced metabolic alterations may be mediated by concurrent changes in the gut microbiota.^28^ Consequently, gut microbiome-targeted therapeutics may help reduce the major end-organ morbidities of OSA. Through metagenomics and metabolomics approaches, we will determine whether gut microbiota play a pivotal role in OSA-related complications, especially in alleviating neurocognitive dysfunction.

To our knowledge, the proposed study will be the first to investigate the effects of CPAP on neurocognitive dysfunction in OSA and to explore the underlying mechanisms using combined ‘-omics’ approaches. The results of this multicentre trial may be helpful for improving the neurocognitive function of patients with OSA.

This protocol describes a multicentre RCT to assess the effects of CPAP treatment on neurocognitive function in patients with moderate to severe OSA. To reduce potential bias, multiple rigorous methods, such as randomisation, blinding of raters and statistical analysers and ITT principles, will be implemented. Potential limitations of this protocol should also be addressed. First, sham CPAP is not used as a placebo; therefore, neither participants nor trial researchers will be blinded to the protocol. Thus, performance bias may be inevitable. Second, although all of the raters have been trained by the same neurologist, there may be heterogeneity in neuropsychological tests in each centre.

In summary, this will be the first multicentre RCT to dynamically observe the effects of CPAP on neurocognitive function and to explore the role of the gut microbiota in neurocognitive dysfunction in OSA. The results of this study will help to clarify potential mechanisms for alleviation of OSA and improvement of neurocognitive dysfunction.

### Trial status

At the time of manuscript submission, the enrolment of volunteers is ongoing.
